### **Definitions**

- **Length of mechanical ventilation** is defined as the duration of invasive respiratory support for all episodes with an endotracheal tube in situ for the first 28 days post randomisation. The outcome will be reported using ventilator free days (VFD). A systematically zero value will be assigned for patients who die to allow important weight to death as the most pejorative outcome.
  - For infants with tracheostomies, ventilation support will be considered completed at the time point when the patient reaches pre-intervention baseline respiratory support levels
- **LCOS** is defined as the inability of the myocardium to provide adequate oxygen delivery (DO2) to the tissue. DO2 measurements are not feasible in daily practice, hence accepted surrogate measures are commonly used. For the purpose of this study, **LCOS** will be defined as[6]:

- blood lactate level greater than 4 mmol/l with an oxygen extraction of greater than 35% (SaO2-SvO2 gradient >35%); within the first 48 hours postoperatively and/or
- high inotrope requirement: Inotrope requirement will be calculated by means of the Vasoactive-Inotrope Score (VIS) (2): VIS = dopamine dose (mcg/kg/min) + dobutamine dose (mcg/kg/min) + 100 x adrenaline dose (mcg/kg/min) + 100 x noradrenaline dose (mcg/kg/min) + 10 x milrinone dose (mcg/kg/min) + 10,000 x vasopressin dose (U/kg/hr). A score ≥15 indicating low cardiac *output syndrome*.
- Initiation of **ECLS** in theatre or postoperatively in intensive care with presence of LCOS
- **Death** within 28 days of the operation
- Length of stay in intensive care
- Hospital length of stay
- Renal failure
- Inhaled NO
- Sedation and delirium scores post surgery
- Functional performance at PICU discharge, at hospital discharge, and during follow-up (in comparison to baseline functional status, if available)
- 1-year follow-up surveys (QoL, Ages and Stages Questionnaire, socioeconomic status)
- 1-year follow-up neurodevelopmental assessment with neuropsychologist (at sites where the funding and infrastructure allows): using Bayley-III, including cognitive, language, motor, social-emotional and adaptive behaviours

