#### 5.1.2 Exclusion criteria

- Signs of persistently elevated pulmonary vascular resistance preoperatively requiring iNO or preoperative intravenous use of drugs involved in the NO pathway such as GTN, within 48 hours prior to CPB (oral sildenafil treatment alone is not an exclusion).
- Patient is on ECLS immediately prior to surgery

- Chronic ventilator dependency
- Concurrent known confirmed bacterial sepsis/septic shock, diagnosed within <48 hours prior to surgery and being actively treated with antibiotics at time of surgery (suspected sepsis treated with antibiotics is not an exclusion criteria unless inotropes are required for treatment of septic shock at time of surgery)
- Preoperative acute respiratory distress syndrome requiring HFOV ventilation <48 hours of surgery
- Patient requires high doses of vasoactive drugs prior to surgery with an inotrope score  $\geq 15$  met within 24 hours prior to surgery: Inotrope requirement will be calculated by means of the Vasoactive-Inotrope Score (VIS) (2):  $VIS = \text{dopamine dose (mcg/kg/min)} + \text{dobutamine dose (mcg/kg/min)} + 100 \times \text{adrenaline dose (mcg/kg/min)} + 100 \times \text{noradrenaline dose (mcg/kg/min)} + 10 \times \text{milrinone dose (mcg/kg/min)} + 10,000 \times \text{vasopressin dose (U/kg/min)}$ .
- Cardiac arrest within one week (7d) prior to surgery
- Emergency cardiac surgery which may preclude obtaining informed consent (defined as acutely required life-saving procedure in a patient unlikely to survive the next hours without the surgery)
- Pre-existing methaemoglobinemia (MetHb > 3%)

NB. Patients that were previously enrolled and randomised into the study with surgical procedure performed that required use of cardio-pulmonary bypass will not get re-randomised. Previously enrolled and randomised patients will undergo the same treatment allocation for subsequent surgeries, unless parents opt out. Rationale: For patients undergoing same procedures, any potentially additive protective impact of NO during CPB on long-term neurodevelopment may become diluted by use of CPB without NO during subsequent procedures. We expect that ca. 10% of all CPB cases <2 years may require subsequent CPB <2 years of age.

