## **Outcome measures**

The definition and detail of calculation of outcome measures can be found in the Supplementary Appendix (Section S2), alongside the Stata scripts written to calculate these outcomes (available on GitHub (16)). Briefly, the outcomes are:

- Primary outcome measure: VFDs within 28 days from start of CPB
- Secondary outcome measures:

- Individual VFD components (i.e. duration of mechanical ventilation, death within 28 days after CPB start)
- Individual and components of composite measure of LCOS, and/or ECLS within 48 hours after CPB start and/or death within 28 days after CPB start;
- Length of PICU stay after CPB start;
- Length of hospital stay after CPB start;
- Process of care measures:
  - Treatment with ECLS within 48 hours after CPB start;
  - Duration of postoperative time spent with open chest including unplanned chest reopening after CPB start;
  - Treatment and duration of treatment using inhalational nitric oxide postoperatively after CPB start;
  - Treatment and duration of treatment of postoperative renal replacement therapy (includes peritoneal and continuous venous-venous haemodialysis) after CPB start;
- Physiological descriptors:
  - Postoperative troponin levels during the first 24 hours postoperatively;
  - Severity and duration of postoperative organ dysfunction; and
  - Postoperative acute kidney injury (AKI) and serum creatinine levels measured during the first 24 hours.

For the purposes of analysis and reporting, LCOS within 48 hours after CPB start, ECLS within 48 hours after CPB start, death within 28 days after CPB start and length of stay in PICU and hospital are classified as potentially patient-important secondary outcomes. The remaining secondary outcomes will be reported to describe patient physiology and processes of care only.

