### 411 *Secondary Outcomes*

412 The main secondary outcome is defined by a composite of presence of LCOS, extracorporeal life support (ECLS), or all-cause death.

- 413 • The presence of LCOS (21) will be calculated as a binary variable by evaluating the relevant data items at the following time-points: admission  
414 to PICU, and after six hours, 12 hours, 24 hours, and 48 hours post-PICU admission, or until the patient is discharged from PICU (whichever  
415 occurs first). Criteria for LCOS include a blood lactate level (arterial where available, if not then venous) >4 mmol/L and the presence of an  
416 oxygen extraction of greater than 35% ( $\text{SaO}_2\text{-ScvO}_2$  gradient >35%), or a high inotrope requirement operationalised as Vasoactive-Inotrope  
417 Score (VIS)  $\geq 15$  (22, 23). If these criteria are met for at least one of the above listed timepoints, the presence of LCOS is confirmed. If individual  
418 data items required for the calculation of LCOS are missing, then the patient will be assumed not to have had LCOS.

- ECLS post-CPB during the first 48 hours after CPB start.
- Mortality is defined as all-cause death within the first 28 days after CPB start.

Additional secondary outcomes include PICU and hospital length of stay, which will be measured from start time of CPB. In patients discharged alive from the PICU to the ward and readmitted within 72 hours the subsequent PICU admission duration will be added to the index admission. Length of stay (both PICU and hospital) will be censored at 28 days or when the patient was last alive, whichever occurs earlier. Patients who die during their PICU or hospital admission will be assigned the time to event.

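### The inotrope score behind LCOS is printed with two vasopressin units that differ 60-fold, and the SAP does not say which applies, so the main secondary outcome is not uniquely defined

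*Combined protocol and SAP*

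**What the plan says.** **Vasopressin unit.** Protocol 5.1.2 excludes children with a VIS of 15 or more "met within 24 hours prior to surgery: Inotrope requirement will be calculated by means of the Vasoactive-Inotrope Score (VIS"). Its last term multiplies by 10,000 the "vasopressin dose (U/kg/min"). Protocol 7.2 (Definitions) prints the same score for LCOS, but its last term is "10,000 x vasopressin dose (U/kg/hr"), followed by "A score ≥15 indicating low cardiac" output syndrome. The other five drugs are per minute in both places, with identical multipliers.

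SAP Supplementary Appendix S2 accepts "a high inotrope requirement operationalised as Vasoactive-Inotrope" Score ≥15 at any one listed time point as sufficient for LCOS. It cites two papers for the score and prints no formula or unit. The SAP section on outcome measures refers for calculation detail to S2 and to Stata scripts, which are not among the documents supplied.

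**LCOS window.** The SAP section on outcome measures classifies "LCOS within 48 hours after CPB start, ECLS within 48 hours after CPB start" among the patient-important secondary outcomes. S2 evaluates LCOS at PICU admission "and after six hours, 12 hours, 24 hours, and 48 hours post-PICU admission". Protocol 7.2 attaches a limit of 48 hours after surgery to the lactate and oxygen-extraction criterion and prints none for the VIS criterion.

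**ECLS.** Protocol 7.2 counts ECLS started "in theatre or postoperatively in intensive care with presence of LCOS" and gives no time limit. The SAP counts ECLS in the first 48 hours after CPB start, with no LCOS condition.

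**The concern.** LCOS was the pilot's clearest finding (35.8% against 12.3% in children under 2 years, Protocol Table 1). It is a component of the composite that S2 names as the main secondary outcome. Two analysts working from these documents could derive different LCOS and composite rates from identical data.

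Three features of the plan make this harder to notice or more influential:

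- Data monitoring compares entered values with source records. It would not reveal a wrong unit inside a derived score.
- S2 treats a child with missing LCOS items as not having LCOS. Where lactate or the saturation gradient is missing, the VIS can decide the classification alone.
- The SAP's planned Figure 3 plots VIS by treatment group, so the unit affects a displayed result as well as a yes/no classification.

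**Working it through.** **The plan's own computed figure.** The only computed design figure is N = 1320, for ventilator-free days. Per arm, 2 × (1.96 + 1.2816)² / 0.2² = 525.4, rounded up to 526. Adding 10% and 15% gives 526 × 1.25 = 657.5, so 658 per arm and 1316 in total; compounding them as 526 × 1.15 × 1.10 gives 666 and 1332. Both are within 1% of 1320. The VIS does not enter this calculation, and the documents state no power for LCOS.

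**The unit.** Inputs: multiplier 10,000 and cut-off 15 (both sections), with 1 U/kg/min = 60 U/kg/hr.

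- Dose giving 15 points from vasopressin alone: 15 / 10,000 = 0.0015 in the printed unit.
- Under 5.1.2: 0.0015 U/kg/min, or 0.0015 × 60 = 0.09 U/kg/hr.
- Under 7.2: 0.0015 U/kg/hr, or 0.0015 / 60 = 0.000025 U/kg/min.
- Ratio: 0.0015 / 0.000025 = 60.

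The doses below only illustrate the arithmetic; the documents give none.

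| Infusion (U/kg/min) | Same infusion (U/kg/hr) | Points under 5.1.2 | Points under 7.2 |
|---|---|---|---|
| 0.000025 | 0.0015 | 0.25 | 15 |
| 0.0001 | 0.006 | 1 | 60 |
| 0.0003 | 0.018 | 3 | 180 |
| 0.001 | 0.06 | 10 | 600 |
| 0.0015 | 0.09 | 15 | 900 |

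From 0.000025 to just under 0.0015 U/kg/min, vasopressin alone stays below the exclusion cut-off yet makes the same child LCOS-positive.

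**What this could do to the LCOS comparison.** Suppose the per-hour version were coded and the per-minute version intended. Let v be the share of otherwise LCOS-negative children who receive vasopressin, assumed equal in both arms. Each observed rate becomes p + (1 − p)v, so the risk difference shrinks by the factor 1 − v. Power is for an unadjusted two-sided 5% comparison of 660 per arm.

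| v (assumed) | Pilot rates 35.8% vs 12.3%: OR | Assumed rates 30% vs 22%: OR | Power, 30% vs 22% |
|---|---|---|---|
| 0 | 0.25 | 0.66 | 91% |
| 2% | 0.28 | 0.67 | 89% |
| 5% | 0.31 | 0.69 | 86% |
| 10% | 0.37 | 0.72 | 79% |
| 20% | 0.45 | 0.77 | 66% |

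Worked line at v = 10%: 0.30 + 0.70 × 0.10 = 0.370 and 0.22 + 0.78 × 0.10 = 0.298, a difference of 0.072 instead of 0.080. At the pilot rates, power stays near 100% throughout.

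**The windows.** PICU admission follows CPB start, so a reading 48 hours after admission always falls more than 48 hours after CPB start. With an assumed gap of 2 to 8 hours it falls at 50 to 56 hours. The conflict therefore decides whether one of the five S2 time points counts. It matters only for children still in PICU at 48 hours whose first positive reading is that one.

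**The case against.** The strongest reply is that this may be a slip in one line that never reached the analysis. The SAP takes the score from cited papers rather than from Protocol 7.2, the calculation sits in code that the documents do not include, and every other VIS term is per minute. That stands as a possibility. A reader might infer that, because the SAP is silent, the per-hour version governs and the main secondary outcome is misclassified. The documents do not support that step; they show only that the rule is not fixed.

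A reader might also infer that LCOS becomes close to a marker of whether a site uses vasopressin. No figure supports this. The documents report no vasopressin use, and LCOS can also be met through lactate with oxygen extraction, or through the other five drugs. Only children on vasopressin who meet no other criterion at any time point would change status.

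Further points in the plan's favour also stand. Randomisation is stratified by site, the LCOS model includes a site effect, and surgical, anaesthetic and ICU staff are blinded, so an error common to both arms would most likely dilute an effect rather than create one. The SAP declares secondary results exploratory. Its main-text outcome list is introduced as a summary and refers to S2, where the LCOS time points are explicit. The ECLS rule is consistent within the SAP. None of this supplies the missing unit.

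**Conclusion.** The contradiction between Protocol 5.1.2 and 7.2 is certain, and the factor of 60 is exact. Because the SAP prints no formula, LCOS, the composite and the VIS plot are not uniquely defined and may be misclassified.

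How many children this affects cannot be computed from the documents. If the per-hour version was coded by mistake, dilution is the most likely effect. That rests on vasopressin use being similar in the two arms among children who are otherwise LCOS-negative. The loss of power ranges from negligible to about 25 percentage points (91% to 66%) under the assumed shares of 2% to 20% and the assumed 30% against 22% effect.

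The LCOS window is a smaller inconsistency inside the SAP. The ECLS difference is a discrepancy between protocol and SAP. A reader might conclude that LCOS and ECLS need one shared window, but components of a composite may have different windows, as death at 28 days already does.

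The primary outcome, its sample size and the interim stopping rule do not use the VIS, so the primary conclusion is not at risk.

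**What to change.** Before unblinding:

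1. Reconcile Protocol 5.1.2 and 7.2 to one VIS formula with one vasopressin unit, and print that formula with its units in SAP S2. Which unit is intended is for the sponsor to establish. If 5.1.2 is the section that changes, record which unit was applied at screening.
2. Check the unit in which vasopressin is entered on the CRF and how the code converts it. Re-derive LCOS, the composite and the VIS plot only if the code departs from the agreed unit.
3. Align the LCOS window in the SAP's outcome measures section with the S2 time points.
4. State one ECLS definition in both documents, with its time limit and whether LCOS must be present.

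The cost is a wording change in each document and a short code check. If the code proves wrong, the derivation is rerun and the LCOS rate may change. The SAP already commits to declaring changes made after its publication.

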### 7.3 Blood Sample Collection for Inflammation analysis

**Biomarker Analysis and Biobanking:** Blood markers for myocardial injury and inflammatory response will be collected on induction of anaesthetics (baseline – pre bypass), at admission to PICU (0 hours – post bypass) and at 12, and 24 hours for the following purposes: i) to test the impact of the intervention on markers of inflammation; ii) to stratify patients in to high- versus low inflammatory groups; iii) to biochemically define responders to the intervention (to identify patient subgroups that are more likely to respond to a specific treatment), iv) to develop improved markers of outcome post cardiac surgery. Collection of blood for biomarker analysis and biobanking is optional and parents will be asked to provide their permission during the consenting process.

**Blood sampling and processing.** *Preoperative baseline* (before onset of cardiac surgery, done by anaesthetist during the induction of the patient once the arterial line has been inserted): 1-2ml of EDTA blood (for DNA), 2.5ml of blood (PAXgene tube for gene expression markers), 1-2ml of serum *Postoperative at 0,12,24 hrs* (in PICU until discharge to the ward): 2.5ml of blood (PAXgene tube - time point 0 only), 1-2ml of serum. The total amount of blood taken is 10-15ml for the entire study duration, which is much less than the amount of blood taken for routine perioperative care tests. The samples will be processed within 30 minutes, centrifuged, aliquotted and immediately frozen. The samples will be kept in a security protected freezer in the each institution, and will be transferred in batch every 12 months to the Centre for Children's Health Research, Brisbane, Australia. Urinary electrolytes and NH4 will be measured from patient urine collected through the

standard IDC at baseline, admission to PICU, and 6-24hours to assess for renal concentration and secretory function. Paired arterial and venous gases will be collected postoperatively at 0,6,12,24,48 hrs (in PICU until discharge to the ward or removal of arterial line, whichever occurs first) to assess for lactate and SaO2-SvO2 gradient. Each arterial or venous blood gas sample requires 0.2mls of blood and would total 2mls across all samples. Routine paired gases are often part of standard clinical care.

#### ***Use of biobanked blood:***

***The following list the specific analyses to be performed using the biobanked blood samples:***

***Cytokine and Metabolomic Measurement and analyses[34-36]:*** Inflammatory cytokines will be measured using multiplex cytokine assay using 50uL of serum on Cytokine Human Ultrasensitive 27-Plex Panel for Luminex® Platform at Diamantina Institute, University of Queensland or similar to higher performant test dependent on availability and prize at completion of the study). For optimal costing batch effect, cytokine measurements will be done at the end of the study in all samples concomitantly. Several candidates have been selected (Levels of systemic inflammatory markers (TNF, Csf2, IL5, IL10, IFNG, IL8, IL4, IL2, IL6, IL1B). Untargeted metabolomics will be performed on plasma samples using liquid chromatography-mass spectrometry with Australian partners such as the Centre for Integrative Metabolomics & Computational Biology (Edith Cowan University). We will identify cytokine and plasma metabolites that discriminates between children with worse outcomes including LCOS and those who do not have these outcomes by assessing the latent multivariate structure of the data using Principal Components Analysis and similar tools. Candidate biomarkers identified in this analysis will then inform the development of a targeted cytokine/metabolite panel.

***Markers of organ dysfunction:*** Markers of cardiovascular (natriuretic peptides, BNP), renal (serum neutrophil gelatinase-associated lipocalin NGAL Nephrocheck (cell cycle arrest biomarkers), IL-18, LFABP, CHEM1, FGF23), and pulmonary damage (soluble receptor for advanced glycation end products (sRAGE)) marker of myocardial injury (Troponin I) where available. Serum samples may be shipped overseas for sample measurement.

***Gene and gene-expression based markers:*** gene changes and gene-expression will be investigated, to test the individual response to the intervention, and to develop improved markers. Gene-expression analyses will be performed on RNA aliquots obtained from the PAXgene Blood RNA tubesRNA will be extracted using PAXgene silica-membrane technology (PAXgene Blood miRNA Kit) on QIAcube extractor at TRI-UQ. Full transcriptome sequencing will be done at the Institute for Molecular Biosciences Sequencing Facility at University of Queensland. Raw Illumina reads will be mapped to the human reference genome. HTSeq-count will be used to count reads mapping to exons, and to estimate fragments mapping per kilobase per million mapped reads (FPKM). A generalised linear model framework in EdgeR will be used to identify differentially expressed genes between disease groups, considering genes with a false-discovery rate (FDR), as estimated by a Benjamini-Hochberg procedure, to be differentially expressed. We will use Fisher's exact test to calculate whether particular Gene Ontology categories or KEGG pathways are significantly enriched

in differentially expressed genes. We will use the weighted gene coexpression network analysis (WGCNA) tool, to identify co-regulated gene modules, and identify differentially expressed modules by association of module 'eigengene' with disease group. We will *derive minimal signatures distinguishing the disease groups* using a rapid forward-selection algorithm we have previously used. The performance of the signatures will be assessed using cross-validation.

**Determination of serum vitamin C levels and their relationship with presence and severity of response to CPB.** The unique dataset and biobank acquired thanks to this study will enable to improve our understanding of response to CPB in children. Specifically, we will investigate whether levels of vitamin C in blood are associated with severity after CPB, as postulated by recent studies who have proposed ascorbic acid as a novel treatment. These tests will be performed in batch in Queensland Health and University of Queensland laboratories. Test results will be available to researchers only and will not affect clinical care as performed in batch for research only purpose. The tests will be done on already available study aliquots and will not increase or alter the amount of study blood taken.

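### Protocol 7.3 aims to find cytokines and metabolites that separate children with worse outcomes, but names only an unsupervised tool and states no outcome link, false-positive control or validation

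*Combined protocol and SAP*

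**What the plan says.** The biobank part of protocol section 7.3 gives one paragraph to cytokines and metabolites. Its aim: "We will identify cytokine and plasma metabolites that discriminates between children with worse outcomes including LCOS and those who do not have these outcomes". Its method: "by assessing the latent multivariate structure of the data using Principal Components Analysis and similar tools". Its use: "Candidate biomarkers identified in this analysis will then inform the development of a targeted cytokine/metabolite panel". The cytokine assay is the "Cytokine Human Ultrasensitive 27-Plex Panel for Luminex" platform, with ten cytokines already listed as candidates. The metabolomics is untargeted, and the number of metabolites is not given.

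The gene-expression paragraph that follows is more specific. It fits a generalised linear model between disease groups, "considering genes with a false-discovery rate (FDR), as estimated by a Benjamini-Hochberg procedure, to be differentially expressed". It relates each co-expression module to disease group, and it closes with "The performance of the signatures will be assessed using cross-validation".

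On sample size, section 7.3 says only: "Collection of blood for biomarker analysis and biobanking is optional and parents will be asked to provide their permission during the consenting process". The SAP (Statistical analysis principles) leaves inflammatory markers to a separate report and gives no method for them.

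**The concern.** The aim is discrimination, which is a statement about marker and outcome together. The one named tool looks at markers only. Its leading components follow the largest shared variation, which may come from age, site or haemodilution rather than from LCOS.

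A reader therefore cannot tell how a marker gets onto the candidate list, how often a list would arise by chance, or whether a marker that truly differs would be found. The candidates inform a targeted panel. Improved markers of outcome are a stated purpose of the blood collection (7.3, purpose iv), and predictors of worse outcome are a pre-planned analysis (3.3). What is at stake is the credibility of that panel, not the main trial result.

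**Working it through.** The plan states no figure for this analysis, so there is none to reproduce. The check compares the two paragraphs and then illustrates what each way of filling the gap would do.

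**1. The two paragraphs in 7.3 side by side**

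| Element | Cytokines and metabolites | Gene expression |
|---|---|---|
| Link to outcome | None stated | Model of disease group; module association with disease group |
| False-positive control | None stated | Benjamini-Hochberg FDR (no cut-off given) |
| Selection rule | None stated | Forward selection of minimal signatures |
| Validation | None stated | Cross-validation |

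Nothing elsewhere fills the first column. Section 11.1 lists generic tests for secondary outcomes, and the SAP says secondary and other outcomes are not corrected for multiplicity.

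**2. What the named tool uses.** Let Z be the standardised marker matrix (n children by p markers). The loadings are the eigenvectors of Z'Z/n. The outcome y does not appear in that formula. If LCOS labels are shuffled between children, every component and loading stays the same.

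**3. False findings when no marker is related to outcome.** Inputs:
- 27 cytokines (7.3).
- LCOS in 12% or 36% of children (pilot Table 1, NO 12.3% and control 35.8%, rounded).
- 300, 600 or 1,000 sampled children (assumed, since sampling is optional).
- Four latent factors (assumed).
- 1,000 simulated datasets in each of the six settings, with LCOS independent of every marker.

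| How the gap is filled | Datasets with a finding | Simple check |
|---|---|---|
| Five largest loadings on component 1 | 100%, by construction | Outcome not used |
| Five component scores compared by outcome, p < 0.05 | 20.9-23.5% | 1 - 0.95^5 = 0.226 |
| 27 markers compared by outcome, p < 0.05 | 62.7-64.9% | 1 - 0.95^27 = 0.750 if independent; 27 x 0.05 = 1.35 false positives expected |
| 27 markers, Benjamini-Hochberg at 5% | 2.9-5.2% | Nominal 5% |

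**4. Missed markers, small panel.** Same 27 markers, 600 children, 25% LCOS (assumed), with one marker unrelated to the others and shifted by 0.5 SD. It was never among the five largest loadings on component 1 in 1,000 datasets. Benjamini-Hochberg testing gave a finding in 98.7%. At least one of five component scores was significant in 99.6%, so in this small panel a score comparison did register a difference.

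**5. Missed markers, large panel.** 600 children, 25% LCOS, 500 markers, five background factors and 20 true markers shifted by 0.4 SD (all assumed; two sets of runs).
- The 20 largest loadings on the first three components held 0 to 2.2 true markers on average. Chance alone gives 20 x 20/500 = 0.8.
- Marker-by-marker tests with Benjamini-Hochberg at 5% found 16.3 to 17.6 of the 20.
- Taking markers from components significant on outcome recovered none of the 20 when they lay outside the main factors. Recovery was good only when they sat together in one factor.
- With no true marker, the Benjamini-Hochberg rule selected 0.1 or fewer markers on average in one set of runs. In the other it selected 0.4 on average, with any selection in 10% of 60 runs.

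**The case against.** A reader might infer that markers are to be picked by their loadings, so that a candidate panel is certain to appear whether or not any marker is related to LCOS. The documents do not support that. The paragraph never says that loadings decide. It names the contrast between children with and without worse outcomes, so comparing component scores between those groups is a fair reading. The other tools it allows are undefined and could include methods that use outcome. The 100% in the table follows from assuming a rule that always returns a fixed number of markers.

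Principal components followed by an outcome comparison can also work. With the same 600 by 500 set-up and the whole largest factor shifted, the 20 largest loadings held 14.2 true markers, and a Bonferroni test of three component scores detected the difference in all 60 runs. With the second factor shifted, the figures were 12.4 of 20 and again all 60. The null rate of that test was 6.3% of 300 runs. The protocol's background describes a broad inflammatory cascade, so a coordinated shift is plausible. The poor recovery in step 5 belongs to sparse effects and does not generalise.

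Nor would the aim on predictors go wholly unanswered: transcriptomics, organ-dysfunction markers and vitamin C are listed separately. The candidates only inform the panel.

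All of this stands. It limits how far the simulations reach. It does not supply the missing outcome link, error control or validation.

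**Conclusion.** The point holds as a mismatch between aim and method. The only named tool is unsupervised and cannot by itself show that a marker discriminates, and the paragraph leaves out three elements that the next paragraph includes.

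The size depends on the unstated rule. For 27 cytokines with no true association, about 21-24% of datasets give a significant component if five scores are compared without correction. The figure is 63-65% if markers are tested singly without correction, and 3-5% with FDR control. Markers outside the main components can be missed in a large panel. These figures rest on the assumed sample sizes, factor structure and effect patterns; the number of sampled children and of metabolites is not in the documents.

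The priority is low. The work is exploratory, uses optional samples, is reported apart from the main analysis, and leaves the primary outcome untouched.

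**What to change.** Amend the cytokine and metabolite paragraph in 7.3, or the separate analysis plan for these markers, before the assay data are examined. Cytokines are measured in one batch at study end, so there is time to do so.

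- **Outcome:** name it. The SAP's composite of LCOS, ECLS or death would serve.
- **Selection:** regress that outcome on each log-transformed marker, adjusted for randomised arm, age group, physiology and site. Take as candidates those with a Benjamini-Hochberg FDR below 5%. A penalised logistic model with selection inside cross-validation is an alternative.
- **Test family:** state which sampling times are used and count them. Serum is drawn at four times, so the cytokines alone could give 27 x 4 = 108 tests.
- **Validation:** report cross-validated performance, as the gene-expression paragraph does.
- **Principal components:** keep them for quality control (batch, site, outliers) and description. If component scores are to be compared by outcome, state how many and with what correction.

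The cost is wording and routine analysis on the same assays, with no extra samples. The downside is a possibly shorter candidate list, and limited power if few families agree to sampling: in the 500-marker illustration, 300 children gave only 6 to 9 of the 20 true markers under FDR control.
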